#### Data analysis

For our primary linkage outcome we will measure the change in proportion of clients linked in two ways: 1) a difference in proportions test comparing the average share of clients linked in the baseline period to the average share of clients linked in the intervention period and 2) a non-parametric interrupted time series (ITS) analysis. For the ITS, the proportion of clients linked will be aggregated quarterly, and the model will be adjusted for covariates including sex, age, race, ethnicity and housing status at jail release, treatment experience prior to incarceration in jail and form of MOUD provided in jail.

For our secondary analysis on retention in care, patients initially linking to SAIA clinics will be matched to patients initially linking to non-SAIA clinics using propensity score matching. Variables used in the propensity score will include sex, age, race, ethnicity and housing status at jail release, treatment experience prior to incarceration in jail and form of MOUD provided in jail, in addition to the baseline period retention rate of the index provider seen following release. Our primary approach will rely on inverse probability weighting with the estimated propensity scores. We will also assess the robustness of our results using a kernel-density-based matching estimator using the propensity scores. Our estimate of interest is the average treatment effect on the treated (ATT).

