### Process for introducing SAIA

SAIA-MOUD’s standard operating procedures (SOP) including the timing/duration, training schedules and intervention component guidelines (MCAT, process mapping and CQI) have been developed and acceptability tested with frontline MOUD staff and managers in the proposed study setting as part of formative work. In the first month of intervention, each facility team (including managers and staff from a range of sectors) will receive an on-site, 2-day orientation from the study team on the SAIA-MOUD SOPs. During this orientation to SAIA-MOUD implementation, facility teams jointly populate and interpret the MCAT, develop process maps of current patient care pathways to initiate or continue MOUD at their sites or referral clinics, and define 1–2 micro-interventions, and indicators to monitor the impact of these modifications.

In the first month of the SAIA-MOUD trial, each facility team will receive two 60-min supervision visits by study personnel, followed by monthly visits throughout the remainder of the 24-month intensive implementation period. During the 12-month sustainment period monthly mentorship visits will be conducted internally by the site team without support from study personnel to evaluate SAIA-MOUD sustainment with moderate resource investment.

Based on the other SAIA adaptations and the development process of the MCAT and its beta testing, we expect that analysis and improvement cycles will occur monthly, with an average of 12 cycles per year per implementing facility.

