#### Exposure definition

Facilities will be considered unexposed prior to SAIA-MOUD intervention starting in their health facility and exposed thereafter. Individuals’ exposure to the intervention will be based on the exposure status of the facility in the calendar month in which they enter care (including those newly identified as eligible for MOUD and those already diagnosed with substance use disorder and on a medication for opioid use disorder).

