#### Power and sample size

Power estimates are for our primary analysis – to detect an impact of SAIA-MOUD on linkage to MOUD referral services within 30 days of release from JHS. Our primary analysis will be a difference in proportions test. Assuming a baseline proportion linked of 22%, and a conservative estimate of 100 people beginning or continuing MOUD in jail and releasing to the community each month (or 2,400 total releases in each of the baseline and intervention periods), we have 80% power to detect a change in the proportion linked of 3.3% percentage points or greater, and 90% power to detect a change in the proportion linked of 3.9% percentage points or greater. Power calculations were performed using the power.prop.test function in R.

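### The primary test and its power statement treat 2,400 releases per period as independent, although exposure changes by facility and calendar month in one jail system; shared month or quarter shocks would make the standard error too small

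*Protocol article*

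**What the plan says.** Under Power and sample size the article states that "Our primary analysis will be a difference in proportions test", with the aim of detecting an impact of SAIA-MOUD on linkage within 30 days of release. The rate input is "Assuming a baseline proportion linked of 22"%. The volume input is "a conservative estimate of 100 people beginning or continuing MOUD in jail and releasing to the community each month", giving "2,400 total releases in each of the baseline and intervention periods". The calculation uses R's power.prop.test and reports detectable changes of 3.3 points (80% power) and 3.9 points (90% power). It has no design effect, intraclass correlation or between-month variance term.

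Data analysis repeats the choice: "a difference in proportions test comparing the average share of clients linked in the baseline period to the average share of clients linked in the" post-introduction period. It then lists a second way of measuring the same outcome, a covariate-adjusted interrupted time series (ITS) on quarterly proportions.

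Exposure definition sets the unit of exposure differently: "Individuals’ exposure to the intervention will be based on the exposure status of the facility in the calendar month in which they enter care". Outcomes gives the two periods as 24 baseline months (January 2022 to December 2023) and 24 months after introduction.

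**The concern.** The contrast is between two blocks of time in one jail system, but the precision is computed as if 4,800 people had each been drawn independently. People released in the same month face the same jail staffing, clinic capacity and policy. If those conditions vary randomly over time, releases within a month are correlated, and a two-sample binomial standard error omits that component.

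This does not need the same person to be released twice, and it does not need a secular trend. It arises with distinct people and a flat long-run linkage level.

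Two things are at stake. An ordinary run of good or bad months could be declared an effect of SAIA-MOUD more often than 5% of the time. And a test that does allow for this variation has less power than the article implies.

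**Working it through.** **Inputs from the article.** Baseline linkage p = 0.22; 100 releases per month; 24 months, so n = 2,400 per period; target changes 3.3 and 3.9 points. Alpha is not stated; 0.05 two-sided is assumed, the default of the named function.

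**Assumed input.** The between-month SD of the true linkage probability, τ, is not in the article. A range of 1 to 3 points is shown.

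**Step 1: the plan's own figures.** With the named function's formula for an increase from 22%, power is 76.8% at 3.3 points and 88.6% at 3.9 points. The detectable changes are 3.44 and 3.99 points. Using the baseline variance p(1-p) in both periods gives 78.8% and 90.3%, closer to the stated 80% and 90%. Both routes use 2,400 independent releases with no inflation. The gap between 76.8% and 80% is a separate matter, so the effect of time clustering is measured from 77% and 3.44 points.

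**Step 2: independent months.** With p(1-p) = 0.22 × 0.78 = 0.1716:

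- ICC = τ² / 0.1716
- Design effect DE = 1 + (100 - 1) × ICC
- Actual false-positive rate of the named test = 2 × [1 - Φ(1.96 / √DE)]
- Detectable change at 80% power: the formula of step 1 with n = 2,400 / DE

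Example, τ = 0.02: ICC = 0.0004 / 0.1716 = 0.0023; DE = 1 + 99 × 0.0023 = 1.23; rate = 2 × [1 - Φ(1.96 / 1.11)] = 7.7%; effective n = 1,950.

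| Monthly SD | DE | False-positive rate, named test | Power at 3.3 points, t test on 24 v 24 monthly proportions | Detectable change, 80% power |
|---|---|---|---|---|
| 0 | 1.00 | 5.0% | 75% | 3.44 |
| 1 point | 1.06 | 5.7% | 73% | 3.5 |
| 2 points | 1.23 | 7.7% | 67% | 3.8 |
| 3 points | 1.52 | 11.2% | 58% | 4.3 |

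Simulation with no effect and no trend agrees: 5.6%, 7.7% and 11.3% at 1, 2 and 3 points.

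**Step 3: shocks that last a quarter.** The cluster is now 300 releases, so DE = 1 + 299 × ICC. At ICC 0.002 (SD about 1.9 points) DE = 1.60 and the rate is 12%. At ICC 0.005 (SD about 2.9 points) DE = 2.50 and the rate is about 21-22%.

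**Step 4: does a replacement hold 5%?** Simulated under quarter-long shocks with no effect:

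- A t test on monthly proportions rejects about 9% at ICC 0.002 and 13% at ICC 0.005.
- A t test on 8 v 8 quarterly proportions (14 degrees of freedom) rejects about 5% at ICC 0, 0.002 and 0.005.
- Newey-West errors (lag 3, normal critical value) on 24 + 24 months reject about 9% even at ICC 0.

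**Step 5: cost when there is no time clustering.** Power at 3.3 points is 77% for the named test, 75% for the monthly t test and 71% for the quarterly t test.

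**The case against.** **The ITS already works on time points.** True, and it matters: the plan does contain an analysis on quarterly proportions in which variation over time can show. But the ITS is listed second, is not the test named as primary and is not powered. It also does not alter the standard error of the proportions test. It is partial mitigation.

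**Unequal monthly rates do not by themselves break the test.** This stands. If the 48 monthly rates are taken as fixed and the question is only whether two period averages differ, the test is not anti-conservative. The inflation needs month effects to be random. That view is required here because the stated aim is an impact of SAIA-MOUD, not a description of two past periods.

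**The size is assumed.** This also stands. No between-month variance is given, and at a monthly SD of 1 point with independent months the harm is small.

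**Stronger readings that the article does not support:**

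- A reader might infer that the roughly monthly improvement cycles ("we expect that analysis and improvement cycles will occur monthly, with an average of 12 cycles per year per implementing facility") inflate false positives. They do not. That variation occurs only under the intervention and only if the changes alter linkage, so it is part of the effect. If SAIA-MOUD does nothing, the cycles add no noise.
- A reader might infer very high error rates, such as 26% or 42%. With independent months these need an ICC of 0.02 or 0.05, and nothing in the article points to values of that order.
- A reader might infer that the cost-effectiveness intervals are too narrow as well. The article gives only the number of bootstrap deviates, not the resampling unit, so this cannot be concluded.

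**Conclusion.** The point holds in a limited form. The primary test and its power statement rest on independent releases, while exposure is assigned by facility and calendar month in one jail system. Any positive random variation shared within a month or quarter pushes the false-positive rate above 5% and makes the stated power too high. The direction is certain given that assumption; the size is not.

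Over the assumed range of 1 to 3 points monthly SD with independent months, the false-positive rate runs from about 6% to 11%. Power at 3.3 points falls from 77% to between 73% and 58%, and the 80% detectable change rises from 3.44 to between 3.5 and 4.3 points. Longer-lasting shocks make it worse, 12-22% in the quarter-long case. This is a correction the sponsor should make; it does not show that the design cannot answer its question.

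**What to change.** Keep the outcome and both 24-month periods. Take the standard error of the primary contrast from time-aggregated proportions with a small-sample reference distribution, for example a t test on the 8 v 8 quarterly proportions that the plan already forms for the ITS. Monthly proportions are acceptable if the baseline data show no autocorrelation. Newey-West errors with a normal critical value are not recommended on a series this short (step 4).

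Estimate the between-month variance and autocorrelation from the 24 baseline months of 2022-2023, which are already past. Then restate the detectable changes under Power and sample size as a range.

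The cost is analysis-plan wording and a little code, with no extra patients or data. The downside is a wider interval, and some loss of power if there turns out to be no time clustering: 75% (monthly) or 71% (quarterly) against 77% at 3.3 points.

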#### Outcomes

In the main outcome – linkage to MOUD services within 30 days of release from jail (primary goal) – we will assess whether the proportion of clients who link to care (ie. receive MOUD at a referral clinic) within 30 days of release increases from the 24-month baseline period (January 2022 through December 2023) to the 24 months post-introduction of the intervention (Table 2). Linkage is defined as MOUD prescription filled or administered at the referral site. Rather than 14 days, 30 days was chosen as the review period of interest in order to capture individuals taking the recently introduced extended release injectable MOUD which are administered monthly. Since implementation preparation activities took place throughout 2024, this baseline period is excluded.

The secondary outcome analysis will assess retention in care within 30 days after initial linkage for patients in the three SAIA-MOUD clinics compared with retention in care within 30 days for all other patients linked to MOUD services in King County. Again, retention is defined as MOUD prescription filled or administered. This patient-level analysis will assess changes in the whether patients returned within 30 days after initial linkage (a binary yes/no variable) and only patients seen by providers seeing at least 10 patients in a year will be included.

Additional exploratory analyses will assess sustainment of our primary and secondary outcomes in the 12 months after our 24-month intensive implementation phase, as well as effect modification by salient client-level factors.

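### The interrupted time series, the only trend-adjusted analysis of linkage, puts at least seven covariates on 16 quarterly points; if they enter as quarterly summaries, almost no residual degrees of freedom remain

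*Protocol article*

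**What the plan says.** The Power and sample size section names the main analysis: "Our primary analysis will be a difference in proportions test". Its power statement (80% for 3.3 points, 90% for 3.9 points, from 22% with 2,400 releases per period) covers that test only.

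The Data analysis section adds a second analysis of the same outcome, "a non-parametric interrupted time series (ITS) analysis". On its unit and adjustment the text reads "For the ITS, the proportion of clients linked will be aggregated quarterly, and the model will be adjusted for covariates including sex, age, race". The full list has seven named covariates: sex, age, race, ethnicity, housing status, earlier treatment experience and the form of MOUD given in jail. The list is introduced by "including", so seven is a minimum.

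The Outcomes section sets a baseline of January 2022 to December 2023 and an intervention period of 24 months. On the year between, it says "Since implementation preparation activities took place throughout 2024, this baseline period is excluded". The 12-month sustainment phase is exploratory.

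The article does not give the number of time points, the time terms, the coding of the covariates, or whether they enter per person or per quarter.

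**The concern.** The difference in proportions has no time term and the linkage comparison has no concurrent control. Any drift in linkage between 2022-2023 and the intervention period is therefore counted as a SAIA effect. The article gives reasons to expect drift: jail initiation of buprenorphine was integrated only in 2021, new resources are flowing into MOUD, and extended-release injectables were introduced recently. Attribution to SAIA thus rests on the ITS, and the cost-effectiveness analysis takes its effect from the same linkage outcome.

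A regression on 16 points with at least seven covariates plus time terms is close to saturated. The estimated level change would then be very imprecise and would depend on which covariates and category codings are kept. Adjusting for quarterly averages also does not adjust for individual case mix.

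**Working it through.** **1. The plan's own figure.** The inputs are 22%, 2,400 per period and two-sided 0.05 (not stated; assumed as the default of the named R function). With constant variance at 22%, the detectable change at 80% power is (1.960 + 0.842) × √(2 × 0.22 × 0.78 / 2,400) = 2.802 × 0.01196 = 3.35 points; at 90% it is 3.88. The pooled two-proportion formula for an increase gives 3.44 and 3.99. The quoted 3.3 and 3.9 are thus reproduced approximately, and the small gap does not affect this point.

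**2. Number of points.** 24/3 + 24/3 = 16 quarters. 2024 adds none.

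**3. Residual degrees of freedom** = 16 − time terms − covariate columns. Three time terms are intercept, trend and level change; a slope change makes four. Eleven columns would arise, for example, with a five-level race variable and a three-level MOUD form: 5 single columns + 4 + 2 = 11. This coding is an assumption.

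- No covariates: 13 (three terms) or 12 (four terms).
- Seven columns: 16 − 3 − 7 = 6, or 16 − 4 − 7 = 5.
- Eleven columns: 16 − 3 − 11 = 2, or 16 − 4 − 11 = 1.

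**4. Detectable level change.** Assumptions: 22% linked, 100 releases per month (300 per quarter), binomial error only, no autocorrelation, covariates unrelated to outcome, and the 2024 gap kept on the time axis. One quarterly proportion has standard deviation √(0.22 × 0.78 / 300) = 2.39 points. The standard error (SE) of the level change is the median over simulated covariate columns. Detectable change = (t at 0.975 + t at 0.80) × SE.

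| Quarterly model | df | SE (points) | t sum | Detectable at 80% |
|---|---|---|---|---|
| No covariates, 3 terms | 13 | 3.35 | 3.03 | 10.2 |
| No covariates, 4 terms | 12 | 3.60 | 3.05 | 11.0 |
| 7 columns, 3 terms | 6 | 4.71 | 3.35 | 15.8 |
| 7 columns, 4 terms | 5 | 5.33 | 3.49 | 18.6 |
| 11 columns, 3 terms | 2 | 7.70 | 5.36 | 41.3 |
| 11 columns, 4 terms | 1 | 10.46 | 14.08 | over 100 |

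A separate simulation that drew the covariates as quarterly means gave 16.3 and 17.9 for the seven-column rows, so about 16-18 is a fair summary.

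**5. Months instead of quarters.** On 48 monthly points, the same method gives 9.5-10.1 points without covariates and 10.3-11.6 with 7 to 11 columns. Without covariates, quarterly aggregation costs little (10.2 against 9.5 with three terms). The damage comes from combining few points with many columns.

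**6. Keeping 2024 as unexposed.** Without covariates, the detectable change falls to about 6 points (5.9-6.2 monthly, 6.2-6.4 quarterly), because the baseline trend is no longer extrapolated across a year.

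**The case against.** **The degrees of freedom are inferred.** A reader might conclude that the plan commits to a model with 1 to 5 residual degrees of freedom. It does not. It does not say that the covariates are aggregated, describes them in person-level terms, and calls the ITS non-parametric, so the segmented time terms are an assumption. Adjusting at person level before aggregation would leave about 12 degrees of freedom. This stands as a limit on certainty. However, the text aggregates the outcome and then adjusts the model, so quarterly summaries are the plain reading. A smoother would normally use at least as many degrees of freedom as a straight line.

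**An unseen SAP may settle it.** Coding and model form can be left to an SAP. But the article itself fixes the unit, the excluded year and the covariate list, and the concern is that combination.

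**The primary analysis is unaffected.** A reader might infer that the primary result becomes uninformative. That is not supported: the ITS is the second analysis, and the powered test does not depend on it. What weakens is the protection against a secular trend.

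**Excluding 2024 might look like a contradiction**, since the Exposure definition says "Facilities will be considered unexposed prior to SAIA-MOUD intervention starting in their health facility and exposed thereafter" and the trial starts in January 2025. It is not one. That section defines exposure status, not the analysis window, and the Outcomes section gives a reason for the exclusion. Keeping 2024 could bias the estimate if preparation changed care.

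**The remedy does not make the ITS sensitive to 3.3 points.** This is correct and should be stated in the plan.

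**Conclusion.** The concern holds in a conditional form. The article fixes 16 quarterly points and at least seven covariates for the only analysis of linkage that can separate SAIA from a secular trend. If the covariates enter as quarterly summaries in a model with three or four time terms, 5 to 6 residual degrees of freedom remain with one column each and 1 to 2 with 11 columns. The detectable level change is then about 16-18 points, or over 40 at 2 degrees of freedom, against about 10-11 without covariates and 10-12 with the same adjustment by month.

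These sizes assume binomial error, no autocorrelation and covariates unrelated to outcome; autocorrelation, or covariates that drift with time, would make them worse. Even a repaired ITS needs roughly three times the 3.3 points quoted for the primary test (9.5 / 3.3 = 2.9), so it can guard against trend only for large effects.

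**What to change.** Fit the ITS at release level (logistic or linear probability), with calendar month as the time variable, a level change and, if wanted, a slope change at January 2025, covariates entered per person, and standard errors that allow for shared month effects and for persons released more than once. Alternatively, use monthly proportions standardised for case mix at person level. State the time terms and what "non-parametric" is meant to cover.

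State next to the power statement that the ITS cannot detect 3.3 points, and give its approximate detectable change.

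Optionally, prespecify a sensitivity run that keeps 2024, with the caveat that preparation activities may have altered care in that year.

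The cost is SAP wording and slightly more analysis work. The person-level data are those the plan already intends to link, although some linkages still depend on state approval. A monthly series is noisier to plot, but quarterly points can still be used for display. The change should be made before intervention-period data are analysed.

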#### Step 1: Understand MOUD performance and identify priority areas for improvement

The MOUD Cascade Analysis Tool (MCAT) uses routine data to provide a rapid view of drop-offs along the MOUD cascade. Two MCATs have been developed and refined for this study. As an analytic tool, the jail-level MCAT provides care staff with a view of the greatest potential for flow improvements through OUD screening➔MOUD referral➔MOUD access➔release on MOUD as well as linkages between jail and MOUD referral clinics (Fig. 2a). Facilitative sub steps including client’s receipt of an exit interview, referral to community-based MOUD clinic, and/or MOUD prescription or carry medication, are captured but do not contribute to the cascade analysis calculation. The clinic-level MCAT offers health teams a view of the greatest potential for flow improvements for individuals exiting jail on MOUD within 30 days through MOUD evaluation➔ MOUD prescription➔ MOUD pick up/administration➔ follow up visit within 30 days of first visit➔ MOUD pick up/ administration (at second visit) (Fig. 2b).

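### The linkage time series adjusts for form of MOUD given in jail and housing at release, both set after jail-level exposure can begin, so it cannot be interpreted alone

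*Protocol article*

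**What the plan says.** The Data analysis section measures the change in linkage in two ways: a two-period difference in proportions, and "a non-parametric interrupted time series (ITS) analysis" on quarterly proportions. For the ITS, "the model will be adjusted for covariates including sex, age, race, ethnicity and housing status at jail release", and the list continues with "treatment experience prior to incarceration in jail and form of MOUD provided in jail". The same variables go into the propensity score for the retention outcome. Table 2 gives a shorter covariate list that does not include form of MOUD.

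Power and sample size names the primary analysis: "Our primary analysis will be a difference in proportions test". No covariate adjustment is stated for it.

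Under Exposure definition, a person's "exposure to the intervention will be based on the exposure status of the facility in the calendar month in which they enter care". Study setting lists Jail Health Services among the four SAIA sites. Step 1 of the strategy says that the jail-level cascade tool "provides care staff with a view of the greatest potential for flow improvements through OUD screening" and on through referral, access and release on MOUD. Outcomes explains that the 30-day window was chosen "in order to capture individuals taking the recently introduced extended release injectable MOUD".

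**The concern.** An adjusted before-after estimate is easiest to read when the covariates are fixed before exposure. Two of those listed are not, at least for people who enter jail care in an exposed month. Form of MOUD provided in jail is an output of the access step that the jail team works on. Housing at release is recorded at the end of the jail stay. If SAIA moves either variable and it affects linkage, holding it fixed leaves only the part of the effect that does not pass through it.

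This matters because the ITS is the only planned linkage analysis that uses the time series. Readers will turn to it to judge whether a before-after gain is more than a trend. The two linkage analyses also differ in two respects at once: one ignores trend and adjusts for nothing, while the other uses the time course and conditions on variables set after exposure. If they disagree, the reader cannot tell which difference is responsible.

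**Working it through.** **1. Order of events.** Exposure is set in the month of entering care (Exposure definition). Form of MOUD in jail is decided after that, and housing at release later still. For new entrants in an exposed month, both follow exposure. For people continuing treatment that they already had, form may largely reflect care before jail.

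**2. Is each a plausible pathway?**
- Form: the Background section counts offering treatment options and administering MOUD among the jail cascade steps, and Step 1 points the jail cycles at MOUD access and release on MOUD. A pathway is plausible, but nowhere stated.
- Housing: no jail SAIA component targets it. Study setting places housing referrals at the community clinics, after release. The Background section mentions social-service connections for jails in general. This is the weaker example.

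**3. The plan's yardstick.** From 22% with 2,400 releases per period, the plan states detectable changes of 3.3 points (80% power) and 3.9 points (90% power). No alpha is given; I assume 5% two-sided. With the variance held at 22% in both periods, SE = √(2 × 0.22 × 0.78 / 2,400) = 0.01196. Then (1.960 + 0.842) × 0.01196 = 3.35 points and (1.960 + 1.282) × 0.01196 = 3.88 points, close to the stated figures. The usual formula for an increase gives 3.44 and 4.00. Nothing below depends on this gap. The figures belong to the primary test, not the ITS, and serve only as a scale.

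**4. Size of what adjustment moves.** Part moved = (shift in form share due to SAIA) × (linkage difference between forms). The document gives neither input, so these are assumptions:

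| Shift (points) | Difference (points) | Part moved (points) | Share of 3.9 |
|---|---|---|---|
| 0 | any | 0 | 0% |
| 5 | 10 | 0.5 | 13% |
| 10 | 10 | 1.0 | 26% |
| 20 | 10 | 2.0 | 51% |
| 20 | 20 | 4.0 | 103% |
| 30 | 20 | 6.0 | 154% |

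**5. Simulation of a pre/post step.** 16 quarters × 300 releases (2,400 / 8), 400 runs, patient-level adjustment, no time slope. In the first two rows the form share shifts by 20 points, linkage differs by 10 points between forms, and the direct effect is 1.9 points.

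| Scenario | True SAIA effect | Without form | With form |
|---|---|---|---|
| SAIA causes the shift | 1.9 + 2.0 = 3.9 | 3.8 | 1.8 |
| The shift is external | 1.9 | 3.8 | 1.8 |
| No shift, direct effect 3.9 | 3.9 | 3.95 | 3.95 |

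Simulation error is about 0.06 points (1.2 / √400). The first two rows generate the same data and give the same pair of estimates. Only the cause of the shift differs, and with it which estimate is right. The data alone cannot settle that.

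**6. Direction.** If the form that becomes more common links less often, the sign reverses. With a 20-point shift, a difference of −15 points and a direct effect of 4 points, the true total is 4 − 3 = 1 point, while the form-adjusted quarterly model gives about 3.9.

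**7. Precision.** When form enters as a quarterly share, it nearly tracks the step. In a quarterly simulation without a slope (20-point shift, quarterly SD of the share 3 points), the SD of the estimate rose from 1.2 to 4.8 points. Adding a time slope left the means essentially unchanged.

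**The case against.** The best counter-argument is that form of MOUD is a confounder worth adjusting for. The extended-release injectable is described as recently introduced, with no link to SAIA. Baseline is 2022–2023, 2024 is left out, and the intervention starts in 2025, so a product spreading across that gap would look like a SAIA step unless form is in the model. This stands. In the external-shift row, the model without form doubles the true effect (3.8 against 1.9). It is why form should not simply be dropped.

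It is also fair that the examples of workflow change under Step 3 do not mention form, and that likely SAIA pathways such as the exit interview, the clinic referral and the prescription or carry medication at release are not named as covariates. They therefore stay in the estimate.

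A reader might infer that the ITS does remove part of the SAIA effect. The document does not support that: nothing in it shows that SAIA shifts form or housing. A reader might also infer that the primary result is biased. It is not affected, since no adjustment is stated for it.

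Sensitivity models are often left to an analysis plan that is not shown. But this covariate list is fixed in the protocol article itself, with no statement of which effect the adjusted model targets.

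**Conclusion.** The point holds in a limited form. The linkage ITS conditions on form of MOUD and, less importantly, on housing at release. For people entering care in an exposed month, both are set after jail-level exposure begins. Form may be a pathway of SAIA, an outside change, or both, and the document does not say which. A single form-adjusted ITS therefore cannot be interpreted alone, and a disagreement with the pre/post test could come from trend or from this adjustment.

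Any magnitude is illustrative: zero if SAIA does not move form, and up to several points if it moves form substantially and form matters for linkage. It rests wholly on assumed shifts and differences, and the sign can go either way.

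**What to change.** In Data analysis, prespecify two versions of the linkage ITS and report them side by side with confidence intervals:

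- **(a)** Adjusted only for characteristics fixed before the jail stay: sex, age, race, ethnicity, prior treatment, and housing at booking if the linked data provide it. Label it as the total change, including any change in form of MOUD.
- **(b)** The same model plus form of MOUD provided in jail and housing at release. Label it as the change not passing through, or not explained by, those variables.

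State that, as far as these variables are concerned, a linkage gain is attributed to SAIA with confidence only where the two versions agree, and that otherwise the range is reported. Keep both variables in the retention propensity score, where the exposure is the clinic reached after release.

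The cost is a few sentences and one extra model run. The ITS conclusion may be less definite if the versions differ, and version (b) may be imprecise if form enters as a quarterly share. Whether housing at booking can be obtained must be confirmed: Data sources names jail booking and homelessness records but not that variable.
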